## Abstract

**Background:**

Restoring community walking remains a highly valued goal for persons recovering from traumatic incomplete spinal cord injury (SCI). Recently, studies report that brief episodes of low-oxygen breathing (acute intermittent hypoxia, AIH) may serve as an effective plasticity-inducing primer that enhances the effects of walking therapy in persons with chronic (> 1 year) SCI. More persistent walking recovery may occur following repetitive (weeks) AIH treatment involving persons with more acute SCI, but this possibility remains unknown. Here we present our clinical trial protocol, designed to examine the distinct influences of repetitive AIH, with and without walking practice, on walking recovery in persons with sub-acute SCI (< 12 months) SCI. Our overarching hypothesis is that daily exposure (10 sessions, 2 weeks) to AIH will enhance walking recovery in ambulatory and non-ambulatory persons with subacute (< 12 months) SCI, presumably by harnessing endogenous mechanisms of plasticity that occur soon after injury.

**Methods:**

To test our hypothesis, we are conducting a randomized, placebo-controlled clinical trial on 85 study participants who we stratify into two groups according to walking ability; those unable to walk (non-ambulatory group) and those able to walk (ambulatory group). The non-ambulatory group receives either daily AIH (15, 90s episodes at 10.0% O_2_ with 60s intervals at 20.9% O_2_) or daily SHAM (15, 90s episodes at 20.9% O_2_ with 60s intervals at 20.9% O_2_) intervention. The ambulatory group receives either 60-min walking practice (WALK), daily AIH + WALK, or daily SHAM+WALK intervention. Our primary outcome measures assess overground walking speed (10-Meter Walk Test), endurance (6-Minute Walk Test), and balance (Timed Up & Go Test). For safety, we also measure levels of pain, spasticity, systemic hypertension, and autonomic dysreflexia. We record outcome measures at baseline, days 5 and 10, and follow-ups at 1 week, 1 month, 6 months, and 12 months post-treatment.

**Discussion:**

The goal of this clinical trial is to reveal the extent to which daily AIH, alone or in combination with task-specific walking practice, safely promotes persistent recovery of walking in persons with traumatic, subacute SCI. Outcomes from this study may provide new insight into ways to enhance walking recovery in persons with SCI.

**Trial registration:**

ClinicalTrials.gov, NCT02632422. Registered 16 December 2015,

## Background

Persons who suffer a traumatic spinal cord injury (SCI) often must confront life-long walking deficits that limit functional independence and quality of life [1, 2]. Several studies show the importance of walking in prevention of and reduction in negative secondary health conditions (e.g., hypertension, diabetes, obesity, and bone loss etc.), greater life expectancy, and improved quality of life after injury [3–6]. Thus, for persons with incomplete SCI, treatments that promote walking recovery are highly valuable and should be prioritized in combating the deleterious sequalae that accompany SCI.

Acute intermittent hypoxia (AIH) is a relatively safe and noninvasive therapy that holds tremendous promise in promoting walking recovery in persons with SCI. Initial studies found repetitive exposures to modest AIH induced endogenous mechanisms of plasticity in respiratory motor nuclei [7, 8] and profound recovery of breathing capacity in rats with incomplete SCI as early as 7 days after injury [9]. This work led to substantial progress regarding the potential of AIH, alone or when combined with task-specific training, to also improve locomotor function following SCI. Prosser-Loose et al. (2012) showed in a rat SCI model that daily (7 consecutive days) AIH coupled with ladder-walking practice resulted in near-complete and enduring improvements in ladder-walking performance (> 4 weeks). Hayes et al. (2014) translated these findings to humans and showed that persons with chronic, incomplete SCI who received daily AIH (5 days) combined with walking practice (daily AIH + WALK) produced functionally meaningful improvements in overground walking endurance not observed with those who received daily AIH alone [10]. Navarette-Opazo later confirmed these results in a separate clinical trial and showed persistent improvements in overground walking occurred when participants with incomplete SCI received more sessions (4 weeks) of AIH combined with walking practice through treadmill training [11].

We suspect that the combination of AIH and gait training leads to an additive therapeutic effect to produce greater walking recovery improvements than either alone. Prior studies show that combinatorial therapies are effective at amplifying the effects of single treatments in persons with SCI [12, 13]. Whereas combined cellular therapies are sometimes successful in rodent iSCI models, such therapies have seldom been combined with motor training in humans due to risks of systemic drug administration [14–16]. AIH is a non-invasive treatment that may serve as a ‘primer’ for SCI rehabilitation. Traditional training therapies often require more than 4 weeks for only modest long-term benefits on function. Thus, there is considerable need for more effective approaches. Repetitive AIH may fill that need and accelerate the impact of more traditional rehabilitation strategies. While past results support this exciting possibility in persons with *chronic* SCI [10, 11], we do not yet know if daily AIH alone or when combined with walking practice has a synergistic effect on improving walking function in persons at earlier stage injuries or with less initial walking ability.

There is tremendous potential for AIH to improve locomotor function via triggering or aiding rapid forms of endogenous plasticity within residual spinal circuitry after SCI [2, 17]. Prior studies have demonstrated how the greatest locomotor recovery occurred in rats with the greatest tissue sparing (> 40%) after spinal cord contusion [18, 19]. However, Basso et al. found that only a relatively small percentage of sparing (< 2%) is sufficient to trigger neural reorganization below the spinal cord injury site to achieve functionally meaningful gains [19]. Spinal plasticity peaks within the first year after injury and thus, offers a window of opportunity for early AIH treatments to help direct neural reorganization in functionally meaningful ways [20–22].

Here, we detail the study protocol of a randomized clinical trial that examines the distinct influences of repetitive exposures (daily) to AIH, with and without walking practice, on overground walking ability in persons with subacute SCI. Using an established AIH protocol known to elicit short-term improvement of walking ability in persons with chronic spinal injuries [10], we plan to examine the potential for an extended AIH protocol to elicit safe and persistent improvements in walking ability.

### Hypothesis and aims

The fundamental hypothesis guiding this study is that repetitive exposure to AIH (10 sessions in 2 weeks) will enhance walking recovery in ambulatory and non-ambulatory persons with subacute SCI, presumably by augmenting neural plasticity through a combination of spontaneous neural recovery and AIH-mediated spinal mechanisms. To test this hypothesis, we are carrying out three specific aims: 1) to quantify the impact of daily AIH (alone) on restoring walking ability in persons with subacute SCI who are initially unable to walk overground, 2) to quantify the beneficial effects of daily AIH with walking practice (daily AIH + WALK) on improving walking ability in persons with subacute SCI who are initially able to walk overground and 3) to determine if the benefits of daily AIH in persons with subacute SCI are without evidence of maladaptive changes and pathology (e.g. hypertension, autonomic dysreflexia, pain, and spasticity) [10, 23].

## Methods

### Study design and setting

We are conducting a double-blinded, placebo-controlled, counter-balanced, randomized phase II clinical trial to assess the effects of daily AIH, with or without walking practice, on walking function in persons with subacute SCI. We are conducting this study at the Spaulding Rehabilitation Hospital with institutional review board (IRB) approval from Partners Human Research Committee and IRB approval from the Shepherd Center (Atlanta, GA).

### Sample size

We plan to study the effects of daily AIH alone and with WALK in N = 85 persons with subacute SCI. The sample size is a sum of participants who enroll in Aims 1 and 2. We established a Consolidated Standard of Reporting Trials CONSORT flow diagram to summarize our trial enrollment, intervention, allocation, follow-up, and analyses [24].

For Aim 1, our sample size computation focused on interventions: daily AIH versus daily SHAM. Data from our previous randomized clinical trial that examined the effects of daily AIH (vs daily SHAM) on walking speed in persons with chronic SCI showed an effect size of 0.84 at our final follow-up. Using this value, our estimated sample size for this aim is N = 34 participants (includes 12% attrition rate), for a sensitive non-parametric comparison of means between interventions to detect a significant difference at power > 0.8 (f = 0.6, F_1,39_ = 4.6; ρ = 0.4, α = .05).

For Aim 2, our sample size computation focused on interventions: daily AIH + WALK versus daily SHAM+WALK. Data from our previous randomized clinical trial that examined the effects of daily AIH + WALK (vs daily SHAM+WALK) on walking endurance (6MWT) in persons with chronic SCI showed a significant increase of total distance walked (131 ± 100 m). Our preliminary data of the effects of daily AIH alone showed an increase of 23.9 ± 18.0 m on the 6MWT. Using these values and under the hypothesis of an additive effect of daily AIH + WALK (vs daily SHAM+WALK, WALK), we anticipate the difference in change of walking distance between daily AIH + WALK vs daily SHAM+WALK or vs WALK will be approximately 100 m. Hence, our estimated sample size for this aim is N = 51 participants (includes 12% attrition rate), for a sensitive repeated measures ANOVA comparing interventions across 3 time points, using a pooled standard deviation of 90 m, to detect a significant difference at power > 0.8 (f = 0.6, F_1,38_ = 4.4; ρ = 0.4, α = .05).

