#### Randomization and stratification

We stratify eligible participants into either an ambulatory or a non-ambulatory group based on their initial walking function. The ambulatory group includes eligible participants who successfully complete one of the following without human assistance: TUG, 10MWT, or 6MWT without human assistance. Participants enrolled in the non-ambulatory group are unable to complete any of these assessments at initial screening. Prior to enrollment of the first study participant, a research statistician generated the balanced, randomization scheme for treatment allocation in both non-ambulatory and ambulatory groups using the R Statistical Package [29]. Using this scheme, the clinical coordinator assigns each participant to their respective treatment group using their alphanumeric identifier.

Although we inform participants about their group, we blind them to the treatment they receive (i.e. daily AIH or daily SHAM). The clinical raters, trainers, and data analysts are also unaware of the treatment that each participant receives during after the trial. We plan to rigorously quantify our blinding methods. Participants guess the breathing intervention received at the end of each treatment day and indicate guess confidence using a Likert scale [30, 31]. Using a contingency table and Fischer’s Exact Test, we will determine if the probability of correct guessing is different from chance. Using multivariate logistic regressions, we also will assess factors that may influence guessing (e.g., adverse events, perceived effects, and sensorimotor changes).

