### Statistical analysis

To advance our understanding and the applicability of daily AIH-induced walking recovery, we plan to test three sub-hypotheses using parametric and non-parametric statistical inferencing. Statistical significance corresponds to a p-value less than 0.05.

#### Hypothesis 1

Daily AIH improves walking recovery in persons with subacute SCI initially unable to walk as compared to daily SHAM. We plan to quantify the success of completing walking skills using our primary outcome measures (i.e., TUG, 10MWT, and 6MWT) by a recovery score of 0–3. We predict that the number of walking skills recovered will be greater for participants receiving daily AIH vs daily SHAM, indicating improved walking ability. We will use a Friedman two-way (factor 1 = intervention: daily AIH, daily SHAM; factor 2 = time: baseline, mid-test, post-test, and follow-ups) repeated measures analysis of variance (ANOVA) by ranks to compare walking recovery between and within groups. If there are significant differences, we plan post-hoc tests for pairwise comparisons [50]. We also anticipate that improvement in walking recovery will correlate with improved SCI-FAI, WISCI and LEMS scores, suggesting clinical relevance of daily AIH as an intervention across various SCI impairment levels.

#### Hypothesis 2

Daily AIH + WALK improves walking ability in ambulatory persons with subacute SCI as compared to daily SHAM+WALK and WALK. We predict a decrease in 10MWT and TUG time and an increase in 6MWT distance relative to baseline following dAIH+WALK (vs. dSHAM+WALK, WALK). We will test three related sub-hypotheses using a linear mixed model with fixed effects [51]. We will use intervention (daily AIH + WALK, daily SHAM+WALK, WALK) and time (day) as the fixed main effects, with subject as random effect, while scores for TUG (time), 10MWT (time), and 6MWT (distance) will be considered as repeated measures. Differences from baseline scores will be compared between and within interventions at mid-test, post-test, and follow-ups. If ANOVAs reveal significant differences, we will use the Tukey-Kramer post-hoc test to identify pairwise differences. If baseline measures are significantly different between intervention groups, we plan to use an analysis of co-variance (ANCOVA) to analyze these data.

#### Hypothesis 3

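### The power above 0.8 claimed for Aim 1 rests on a walking-speed effect in chronic SCI, but Aim 1 analyses a 0-3 recovery score in subacute participants who cannot complete a walking test at screening

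*Protocol article*

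**What the plan says.** The Sample size section bases Aim 1 on the sponsor's previous randomized trial: "effects of daily AIH (vs daily SHAM) on walking speed in persons with chronic SCI showed an effect size of 0.84 at our final follow-up". From that value it states: "our estimated sample size for this aim is N = 34 participants (includes 12% attrition rate". The comparison is described as non-parametric, and the calculation is summarised as "to detect a significant difference at power > 0.8 (f = 0.6, F_1,39_ = 4.6; ρ = 0.4, α = .05".

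The people and the outcome of Aim 1 are defined elsewhere in the article:

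- Hypothesis and aims: Aim 1 concerns subacute SCI in people who at first cannot walk overground.
- Randomization and stratification: "Participants enrolled in the non-ambulatory group are unable to complete any of these assessments at initial screening". The assessments are the TUG, 10MWT and 6MWT.
- Outcome measures and Statistical analysis (Hypothesis 1): success on these tests is scored 0 to 3 and analysed with a repeated-measures ANOVA by ranks over baseline, mid-test, post-test and follow-ups. The prediction reads: "We predict that the number of walking skills recovered will be greater for participants receiving daily AIH vs daily SHAM, indicating improved walking ability".
- Background: it is not yet known how daily AIH acts on walking at earlier stages of injury or with less initial walking ability.

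**The concern.** The planning effect and the planned analysis differ in injury phase, in walking ability at entry and in outcome scale. A standardised difference in a continuous speed is divided by the spread of speed among people who have one. The Aim 1 score has four levels, and participants enter unable to complete any of the tests being scored. If many stay at one end, ties reduce what a rank test can separate, and 0.84 standard deviations of speed has no direct meaning on that scale.

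Borrowing from chronic SCI would, by itself, be an ordinary planning limitation. Here the outcome changes as well, the article gives no bridging argument, and its Background treats the transfer as an open question. Yet the power is stated without qualification. At stake is how a non-significant Aim 1 result is read: a reader who relies on power above 0.8 would take it as stronger evidence against benefit in non-walkers than the plan supports.

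**Working it through.** **Inputs from the article.** Effect 0.84 (metric not named; read as Cohen's d), ρ = 0.4, α = 0.05 (taken as two-sided), 12% attrition, N = 34, balanced allocation (taken as 1:1). The number of time points is not given for Aim 1. Three is borrowed from the Aim 2 calculation.

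**Step 1: the stated N.** For two equal arms f = d/2 = 0.84/2 = 0.42. For the between-arm effect averaged over m visits,

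λ = f² · N · m / [1 + (m − 1)ρ].

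With N = 30 and m = 3: λ = 0.1764 × 30 × 3 / 1.8 = 8.82. The critical F(1, 28) is 4.20 and power is 0.818. Thirty is the smallest even total that reaches 0.8. Attrition: 30 × 1.12 = 33.6, so 34 (or 30/0.88 = 34.1, so 35). N = 34 is therefore reproducible from 0.84 if three visits are averaged and the outcome is continuous. With one visit, λ = 0.1764 × 30 = 5.29 and power is 0.60.

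**Step 2: does 0.84 belong to Aim 1?**

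| | Source of 0.84 | Aim 1 |
|---|---|---|
| Injury phase | chronic | subacute |
| Walking at entry | had a speed to analyse (inferred from the outcome) | cannot complete TUG, 10MWT or 6MWT at screening |
| Outcome | walking speed | recovery score, 0 to 3 |
| Analysis | standardised difference | ranks, repeated measures |

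No row matches. The article gives no expected distribution of the score in either arm, so power on the planned endpoint cannot be computed from it.

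**Step 3: illustration.** The assumptions are mine: 34 × 0.88 = 29.9, so 15 completers per arm; a normal latent variable with a shift of 0.84, constant over visits; latent correlation 0.4; a four-level score cut from it; and a two-sided Mann-Whitney test on each participant's average as a stand-in for the planned rank analysis. Simulated power:

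| SHAM at lowest level | Three visits averaged | One visit |
|---|---|---|
| no floor (continuous) | 0.78 | 0.56 |
| 50% | 0.75 | 0.51 |
| 70% | 0.74 | 0.48 |
| 80% | 0.69 | 0.43 |
| 90% | 0.59 | 0.32 |

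Repeat runs agree to within about 0.03 (at 70% with three visits, 0.71 to 0.74). With five visits averaged, power is about 0.83 with no floor and about 0.70 at a 90% floor.

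**Step 4: separating the causes.** With three visits the score and floor cost 0.78 − 0.75 = 0.03, then 0.04, 0.09 and 0.19. Dropping from three visits to one costs 0.78 − 0.56 = 0.22 before any floor is applied. For floors of 50% to 80%, most of the single-visit shortfall thus comes from using one visit; at 90% the two causes are of similar size.

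**The case against.** The strongest reply has four parts.

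- *Repeated measures restore power.* Largely true. Aim 1 plans several visits, and with three averaged the loss is modest up to an 80% floor; with five it is smaller. A reader might look at single-visit power of 0.3 to 0.5 and conclude that Aim 1 is badly underpowered. The documents do not support that, because Aim 1 is not planned as a single-visit test.
- *The floor is assumed.* Also true. The article expects spontaneous recovery and follows participants to 12 months, so the floor may shrink. A reader might infer that the trial can detect only very large effects, for example by reducing the score to regained or not regained and applying Fisher's exact test. No such endpoint or comparison is planned for Aim 1. The effect in non-walkers might also exceed 0.84: with a latent shift of 1.2 (the printed f = 0.6 doubled), even single-visit power is about 0.81 with SHAM spread evenly over the score, 0.74 at an 80% floor and 0.65 at 90%.
- *The source is disclosed and better data may not exist.* This excuses using 0.84 as a rough guide. It does not justify stating power above 0.8 as a property of the planned analysis.
- *An article may leave the bridging argument to the full protocol.* It may. But this article states a basis and a power figure, and the stated basis does not fit the stated endpoint.

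Two limits on wording follow. The rule that selects non-walkers is the stratum definition; the eligibility table is not shown, so nothing can be said about it. And participants lack a completed walking test at screening, not necessarily later.

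**Conclusion.** The point holds as a mismatch between the planning effect and the planned analysis. The power claimed for Aim 1 belongs to another outcome in another population, and nothing in the article carries it across. It is not a finding that N = 34 is miscalculated: the figure can be reproduced from 0.84 under the three-visit assumption. Nor is it a finding that power has a particular low value, since neither the direction nor the size of the error can be fixed from the article. Under the illustrative assumptions, with the speed effect carried over in full and three visits averaged, power lies slightly below 0.8 for moderate floors and near 0.6 if 90% of SHAM stay at the lowest level.

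The printed f = 0.6 and the F with 39 error degrees of freedom do not agree with 0.84 and N = 34. That is a separate matter, and the conclusion here does not depend on it.

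**What to change.** Keep N = 34. In the Sample size section:

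1. Remove power above 0.8 as a consequence of the 0.84 walking-speed effect. The earlier trial can still be cited as background.
2. Justify Aim 1 on the 0-3 recovery score in non-walkers under the planned repeated-measures rank analysis. State the number of visits used and the correlation assumed.
3. Give power, or the smallest difference detectable with 80% power, over a range of SHAM score distributions labelled as assumptions.
4. State that a non-significant Aim 1 result does not exclude a moderate benefit.

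The cost is a short recalculation and a change of wording, with no added participants and no change to conduct. The drawback is that the stated figure is likely to look less favourable, and it will rest on assumed distributions unless data on the score in non-walkers become available.

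### Aim 2 is sized on one unadjusted contrast over three time points; its power above 0.8 does not carry over to the three-arm Tukey-Kramer comparisons at single visits

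*Protocol article*

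**What the plan says.** The Sample size section of the protocol article states: "For Aim 2, our sample size computation focused on interventions: daily AIH + WALK versus daily SHAM+WALK". It expects the same effect against either comparator: the difference in change of distance on the six-minute walk "vs daily SHAM+WALK or vs WALK will be approximately 100 m". The calculation rests on a repeated measures ANOVA over three time points, "using a pooled standard deviation of 90 m", "to detect a significant difference at power > 0.8". The printed parameters are f = 0.6 and "F_1,38_ = 4.4; ρ = 0.4, α = .05". The total is 51 participants, including 12% attrition. No adjustment for a third arm is stated.

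Under Statistical analysis, Hypothesis 2 says that AIH+WALK improves walking compared with both SHAM+WALK and WALK. The model is a linear mixed model with the three interventions and time as fixed main effects and subject as a random effect. On the comparisons it says: "Differences from baseline scores will be compared between and within interventions at mid-test, post-test, and follow-ups". On multiplicity it says: "If ANOVAs reveal significant differences, we will use the Tukey-Kramer post-hoc test to identify pairwise differences".

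**The concern.** The sample size is justified with one contrast at an unadjusted 0.05. The conclusion is to be drawn from all-pairs comparisons of three arms, which use a stricter threshold. One of the three pairs covered by that adjustment, SHAM+WALK vs WALK, is not part of Hypothesis 2.

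The sizing also gains precision from three time points, whereas the analysis section describes comparisons at separate visits. If conclusions are drawn visit by visit, the reader cannot assume power above 0.8, even if 100 m and 90 m are exactly right. This matters because the Discussion presents lasting benefit as the goal of the trial, and that is a question about particular follow-up visits.

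**Working it through.** **Inputs.** From Sample size: difference 100 m, SD 90 m, N = 51 including 12% attrition, alpha 0.05, three time points, correlation 0.4. From Randomization and stratification: a balanced scheme. Assumptions: 1:1:1 allocation, two-sided testing, and 90 m as the SD of change (the article says only that it is pooled).

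**Evaluable participants.** 51 × 0.88 = 44.9, so about 45, or 15 per arm.

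**Reproducing the stated power.** The standardised difference is d = 100/90 = 1.11. With n = 15 per arm the noncentrality parameter is d × √(n/2) = 1.11 × √7.5 = 3.04.
- Two groups, one visit, 28 df: power 0.836.
- Average of three visits with correlation 0.4: the variance is multiplied by (1 + 2 × 0.4)/3 = 0.6, so the SD is 90 × √0.6 = 69.7 m and d = 1.434. Power is 0.966.

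Both exceed 0.8, so the stated bound reproduces. The exact calculation behind it cannot be recovered from the printed parameters. The printed f = 0.6 is 100/(2 × 90) = 0.556 rounded up. Error df of 38 imply 40 participants in a two-group contrast, whereas 15 per arm leave 30.

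**Applying Tukey-Kramer over three arms (42 error df).** The critical t is q(0.95; 3, 42)/√2 = 2.43, against 2.02 unadjusted.

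| Comparison, 15 per arm | Unadjusted | Tukey-Kramer |
|---|---|---|
| AIH+WALK vs SHAM+WALK, one visit, d = 1.11 | 0.84 | 0.73 |
| Same, with the printed f = 0.6 (d = 1.2) | 0.89 | 0.80 |
| Same, averaged over three visits (d = 1.434) | 0.97 | 0.93 |
| Both AIH+WALK contrasts, one visit, d = 1.11 (simulated) | 0.75 | 0.60 |

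Requiring a significant omnibus test first hardly changes the single-visit figure (about 0.72 to 0.73).

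**Sensitivity of the single-visit Tukey-Kramer figure.**
- No attrition (17 per arm): 0.79.
- 90 m as a raw-score SD, plain change scores: the SD of change is 90 × √(2 × (1 − 0.4)) = 98.6 m, power 0.64.
- 90 m as a raw-score SD, baseline as covariate: the SD is 90 × √(1 − 0.16) = 82.5 m, power 0.81.

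**Sensitivity of the averaged figure.** The 0.93 needs the full 100 m at all three visits. If the mid-test showed half of it, the average would be (50 + 100 + 100)/3 = 83.3 m, d = 83.3/69.7 = 1.195, and Tukey-Kramer power would be 0.80.

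**Size needed.** At one visit with d = 1.11, Tukey-Kramer power passes 0.8 at 18 evaluable per arm (0.817). That is 54 evaluable, and 54/0.88 = 61.4, so 62 randomised.

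**Fixed sequence at two-sided 0.05, one visit (simulated, pooled three-arm variance).** First contrast 0.84; both contrasts 0.75.

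**The case against.** A reader might infer that the sized contrast has power 0.73 and that the article's claim of more than 0.8 is an arithmetic error. The article does not support that. It did not size a single-visit t-test; it sized a repeated measures ANOVA over three time points, and under that model Tukey-Kramer power is about 0.93. With the printed f = 0.6, power is 0.80 even at one visit. The three-arm omnibus test has power of about 0.87 at one visit. The stated bound survives on its own terms.

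The analysis section can also be read in more than one way. It names intervention and time as main effects and writes no interaction, and a contrast on an intervention main effect pools the visits. The Tukey-Kramer sentence names no visit. A statistical analysis plan that is not shown may settle this.

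A reader might further infer that the plan fails a promise about the joint claim against both comparators. The sample size makes no such promise: it focuses on one contrast. The 0.60 describes how Hypothesis 2 is worded, not a broken power statement.

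All of this stands against calling the stated power false. It does not remove the mismatch. The sentence that compares changes at mid-test, post-test and follow-ups is in the article, and no time-averaged contrast is specified there. The 0.93 also depends on the full effect being present at each of three visits that the article does not identify. The rounding to f = 0.6 corresponds to 0.6 × 180 = 108 m, which is more than the 100 m the article states.

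**Conclusion.** The concern holds as a mismatch between sizing and analysis. The sample size for Aim 2 makes no allowance for the three-arm Tukey-Kramer comparisons. At the article's own 100 m and 90 m, with 15 evaluable per arm, power above 0.8 holds for a contrast averaged over three visits with full effect (about 0.93). It does not hold at a single visit (about 0.73, or about 0.60 for both AIH+WALK contrasts).

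These figures assume equal allocation, two-sided testing and 90 m as the SD of change. Other readings of the SD and of f move the single-visit, single-contrast figure between 0.64 and 0.81. The finding is that the stated power does not carry over to the per-visit tests, not that it is miscalculated.

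**What to change.** In Hypothesis 2, replace all-pairs Tukey-Kramer with a fixed sequence at two-sided 0.05. Test AIH+WALK vs SHAM+WALK first, which is the contrast the trial is sized for. If it is significant, test AIH+WALK vs WALK. Report SHAM+WALK vs WALK descriptively. No omnibus test is needed beforehand. Within one outcome and visit, this controls the error rate over the two hypothesised contrasts, and per-visit power rises to 0.84 for the first and 0.75 for both.

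The change needs no extra participants or data, but it alters the analysis of a trial that began in 2016, so it should be documented as an amendment made before unblinding. SHAM+WALK vs WALK loses its formal test, and AIH+WALK vs WALK is tested only if the first contrast succeeds. Multiplicity across the three primary outcomes and the visits is not addressed by this change.

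If Tukey-Kramer is kept, state in Sample size that power above 0.8 applies to the time-averaged contrast and that single-visit power is about 0.73 at 100 m and 90 m. This costs only a less favourable statement.
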